### Trial Design

The trial is designed using the Standards for Reporting of Diagnostic Accuracy Studies 2015 guidelines. This prospective, randomised, cross-over trial aims to provide a fair comparison between the two tracers in order to establish non-inferiority of the new tracer (^18^F-PSMA-1007) compared to the standard of care in Switzerland (^68^Ga-PSMA-11).

The trial is of open label design, insofar as the investigators will know which radiotracer was used: the normal biodistribution of the two tracers is different, for example, as described above ^68^Ga-PSMA-11 undergoes renal excretion, whereas ^18^F-PSMA-1007 shows little relevant renal excretion in the first two hours. Any trained nuclear medicine physician will be able to recognise the tracer-type immediately. A closed label design is therefore not practicable.

#### Design

The study is designed as a non-inferiority study with n=100 patients. To allow a representative mix of patients that reflect clinical reality, we include patients with any PSA value (the only requirement is that they have a confirmed biochemical recurrence, i.e. PSA > 0.2 ng/ml post prostatectomy).

### Imaging Procedures

Imaging will be performed on the same scanner for all patients at the clinic for nuclear medicine, university hospital Bern. PET scans will be obtained using standard parameters for the scanner type. All examinations will be documented as per clinical routine. The trial physicians when reading the scans will be blinded to this report and the clinical details of the patient.

*6.1.2.1 Imaging Protocol*

Patients will receive standard PET/CT acquisitions as per institutional imaging protocol at 2h p.i. For n=10 individuals, additional dynamic imaging will be performed from the time-point of injection to 80 min (dynamic scans)

*6.1.2.2 Details of analysis*

1. A total of 6 readers will be allocated to the study. 3 readers will be allocated to read all scans for one tracer, 3 readers will be allocated to read all scans for the second tracer. This ensures that both radiotracers are interpreted separately. The odd number of readers allows for simple-majority voting in case of disagreement (i.e. where one reader rates the scan as negative and two others positive).
2. All readers will be experienced in reading scans with their respective tracer type (minimum 100 clinical scans). A training set of literature will be provided to all readers before the study commences, informing the reading physicians about potential pitfalls and normal distribution of both tracer types.
3. Visual analysis will be done according to previously published reading criteria (e.g. PSMA-RADS) to include pathological, non-pathological and diagnostically uncertain lesion types [21].
4. Reading will be done by the readers in a blinded, randomised fashion. The scans will be read at independent reading sessions. No reader will have access to the other readers’ results or interpretation.
5. Readers will report the number of lesions by lesion type (PSMA-RADS 1.0) and by region, as described above.
6. Both readers will record tracer uptake (SUV) and determine lesion to background ratio, which is defined as lesion SUV (peak) ÷ SUVmean of background reference region (defined by convention as the left gluteal musculature).
7. The principal investigator and his team will perform an unmasked scrutiny of medical records to 6-months post the second exam. Where available, a composite standard of correlative imaging, histology and prostate specific antigen will be compared affording a descriptive analysis of lesion-based diagnostic accuracy.

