## Other Outcomes of Interest

In a second round of tumour classification, two readers (in consensus) will classify each lesion as pathological, benign or uncertain in a lesion-specific approach and perform a lesion based follow-up to assess PPV on the lesion level. This would be impossible to determine using a non-consensus multi-reader approach: lacking a coordinate system for the human body which could unequivocally describe each lesion.

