### Follow up procedures

Following the last PSMA-PET/CT, records will be scrutinised at twelve months of clinical follow up. Lesion validation will be performed using a composite standard of histology and/or correlative imaging as well as PSA-dynamics following external radiation therapy where available, affording a descriptive analysis of lesion-based diagnostic accuracy.

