### Response Criteria

Response to targeted treatment (surgery, radiotherapy) will be considered as confirmatory in the case of a fall in PSA, using previously published response criteria [22]. Where PET scan findings are recorded as positive, but the follow up refutes this, the scan will be recorded as false positive. Established RECIST (Vers 1.1) criteria will be used to interpret correlative imaging [23]. The details are as follows:

Follow up of clinical notes to 6 months will be performed for histopathological data, additional conventional imaging (CT, MRI and or bone scintigraphy), PSA change following focal salvage therapy (where no systemic therapy has been applied. Follow-up imaging will be performed by local read.

1. **Follow up histology**

Positive biopsy or histology will be taken to be confirmatory.

For negative biopsies: to rule out false negative imaging for image-guided biopsy will be reviewed. For lymph node biopsies, comparison of the PET/CT and follow-up (post intervention) imaging will be made to confirm that biopsy of the correct node occurred.

1. **Follow up imaging**

No established imaging criteria are available for a number of imaging modalities in recurrent prostate cancer. To enable comparison of these data with previous imaging trials, the imaging criteria as previously published by Fendler et al. will be used (§2.1.5.3 of Supplementary Materials 2: Trial Protocol [24])

1. **Follow up following local treatment**:

PSA change following radiation therapy will be according to previously published criteria, with a PSA response of > 50% taken to be confirmatory [25] (see figure 4).

[figure not shown]

**Fig.4.** Example interpretation criteria for patients undergoing biopsy or radiotherapy (with and without systemic hormone deprivation therapy) image from Emmett et al. [25]

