### Blinding procedures

Data collection will occur as follows:

1. Each individual patient will be assigned a unique patient identifier. Only the sponsor will have access to the “key”.

2. Imaging data will be coded and collected centrally by the sponsor. Coded and randomised data-sets will be provided to the readers at separate reading sessions. Data will be recorded separately on the CRF and the readers will not have access to each other’s results.

3. Once all data has been collected and the centralised reading is closed by the sponsor, the patient details will be unblinded to allow data analysis and clinical follow-up by the PI and his team of physician-investigators as named above.

4. The investigators will read each scan in a blinded fashion, and separately. The investigators will not have access to each other’s results.

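### Findings are verified unmasked after the central reads close, and nothing withholds the tracer-specific calls from the team that sets the PPV reference status

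*Protocol*

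**What the plan says.** Section 6.1.2.2, item 7, assigns verification to the principal investigator and team, who "will perform an unmasked scrutiny of medical records to 6-months post the second exam" and compare the findings with imaging, histology and PSA where these exist.

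Section 6.2.2, item 3, fixes the order of work: the reads are finished first, and only then, in its words, "the patient details will be unblinded to allow data analysis and clinical follow-up by the PI and his team of physician-investigators". Follow-up and data analysis thus fall to one team, after the reads exist.

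Section 6.1.1 states that "the investigators will know which radiotracer was used". Section 6.1.3 describes the reference standard: "Lesion validation will be performed using a composite standard of histology and/or correlative imaging as well as PSA-dynamics" after external radiotherapy. Section 6.1.4 adds the rules: positive histology confirms; PSA change after radiotherapy is judged "with a PSA response of > 50% taken to be confirmatory"; RECIST 1.1 and published imaging criteria apply to later imaging, which is read locally.

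Section 11.4.2 turns the verified status into a PPV per tracer and compares the tracers by McNemar's test and a risk difference. For the separate lesion-level outcome in section 5.3, the two consensus readers classify the lesions and also "perform a lesion based follow-up to assess PPV on the lesion level".

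**The concern.** A reference standard should be set without knowledge of the test result that it is meant to check. Here the people who decide whether a finding was true work unmasked, after the reads have closed, and also analyse the data. In a borderline case, knowing which tracer's panel called the region could tip the decision.

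The comparison at stake is not trivial. The primary endpoint is a positivity rate, so a false-positive patient counts the same as a true-positive one. Section 3.4 notes that non-prostatic uptake is reported as increased with the new tracer and treats this as highly relevant clinically. PPV, by region and in the exploratory lesion-level version, is the only planned outcome that tests whether positive findings are real.

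**Working it through.** No stated figure depends on this point. The power calculation in section 11.2 concerns the primary endpoint, which does not use the reference standard. The check is therefore a reading of the sections together, plus a short piece of algebra.

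**1. What the verifiers may know.**
- Section 6.2.2 releases patient details, which the team needs in order to open the records. It neither releases nor withholds the panel reads.
- Section 9.2.2 applies follow-up to lesions already rated pathological, and section 6.1.4 records a false positive where the PET was positive and follow-up refutes it. Both start from the PET call.
- Section 12.2.3 has the principal investigator collate all case report forms at the end of the study.
- No section provides a masked or independent adjudicator.

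Knowledge of the call is therefore a strong inference, but not stated text.

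**2. Where judgement enters (section 6.1.4).**

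| Component | Fixed rule | Room left |
| --- | --- | --- |
| Positive histology | Confirms | Little |
| Negative biopsy | Reviewed; for nodes, PET/CT is compared with later imaging to see whether the right node was sampled | Clear judgement |
| Later imaging | RECIST 1.1 and published criteria, local read | Some; the protocol itself says that several modalities lack established criteria |
| PSA after radiotherapy | Response above 50% | The threshold is fixed, but PSA is measured per patient and must be credited to a region |

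**3. What reaches the PPV difference.** I take the endpoint as region-based, as in the synopsis and section 5.2; section 11.4.2 writes lesion-based. Among regions with a known status, let *n* be called by both tracers, *a* by the new tracer only and *b* by the old only. Let *x*, *y* and *z* be the numbers confirmed in these three groups. If each region carries one status:

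PPV(new) − PPV(old) = (x + y)/(n + a) − (x + z)/(n + b)

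With a = b = m this becomes (y − z)/(n + m), and *x* cancels. A steered decision in a region called by both tracers then has no effect; only discordantly called regions matter. If *a* and *b* differ, one steered decision in a shared region moves the difference by only 1/(n + a) − 1/(n + b). One in a discordant region moves it by a full 1/(n + a) or 1/(n + b). The plan does not state the one-status rule on which this rests.

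**4. Can a size be given?** The only overlap figure is the planning assumption in section 11.2: 80% positive on each tracer and 75% on both. Hence 0.75/0.80 = 0.9375, so 6.25% of the patients positive on one tracer would be negative on the other. That suggests limited discordance between patients. It does not give *a*, *b* or *n*, because a patient can be positive on both tracers in different regions, and because verification occurs only where clinical care provides it (section 9.2.2). How often verified regions are ambiguous, and which way they would be decided, is not stated anywhere.

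**The case against.** The strongest reply is that the text does not say what a reader might infer from it, namely that lesions are judged in the knowledge of which tracer called them. Section 6.2.2 unblinds patient details only, and since the sponsor alone holds the key (item 1), the records could not be opened otherwise. This stands: the knowledge is inferred. What survives is that nothing prevents it. For the exploratory outcome in section 5.3, classification and follow-up by the same two readers come close to making it explicit.

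Second, histology, the PSA threshold and published imaging criteria leave less room than a free judgement would, and the local imaging read is not assigned to the principal investigator's team. This also stands, and it narrows the problem to the three areas of judgement shown above.

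Third, the design is openly unmasked, and sections 6.1.2.2, 6.1.3 and 9.2.2 call the verification descriptive or explorative. That is a fair reason for low priority. It is not a reason to leave the order of work as it is, because a formal between-tracer comparison is still planned.

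**Conclusion.** The point holds as a cheap improvement, not as an error. The reference status for the between-tracer PPV comparison is set unmasked, after the reads close, by the team that also analyses the data, and no rule keeps the panels' calls from it.

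The effect is confined to PPV; the primary non-inferiority conclusion and its power are untouched. Neither size nor direction can be derived. A reader might infer that the new tracer is favoured, or by how many percentage points, but the protocol gives no basis for either. The statement that only discordantly called regions matter assumes one status per region and similar numbers of called regions for the two tracers.

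**What to change.** In section 6.1.2.2 (item 7) and section 6.2.2 (item 3), state that:
- the team records one reference status per patient and region (positive, negative or unknown) from histology, later imaging and PSA;
- this status is locked before the panel reads are released to the team or linked to the patient, so the collation of forms in section 12.2.3 follows the lock;
- the single locked status is applied to both tracers in the region-based PPV.

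Patient identity can still be released for the record review; only the reads are held back.

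**Cost.** No extra staff: the data are already coded, and section 12.1.1 already restricts access to the electronic forms. A status would be entered for all regions rather than only those rated pathological, at most 5 × 100 = 500 entries, many of them unknown. Section 9.2.2 would need matching wording.

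**Downsides.**
- Masking is partial: both scans are reported clinically and those reports stay in the records, and the node-biopsy check needs the PET/CT, from which the tracer is recognisable (section 6.1.1).
- A region-level status can credit a call when a different lesion in that region is the one confirmed.
- The exploratory lesion-level PPV (sections 5.3 and 9.2.3) is not covered and would need its own rule.

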#### Clinical Procedures

Both scans will be reported as per clinical routine. The scans are provided separate to the clinical trial by physicians not involved in the trial (i.e. none of the 6 readers will be involved in routine clinical care of the patients). In this way, the clinical treatment of the patient will not be adversely affected or delayed by participation in the trial.

### Follow up procedures

Following the last PSMA-PET/CT, records will be scrutinised at twelve months of clinical follow up. Lesion validation will be performed using a composite standard of histology and/or correlative imaging as well as PSA-dynamics following external radiation therapy where available, affording a descriptive analysis of lesion-based diagnostic accuracy.

### Response Criteria

Response to targeted treatment (surgery, radiotherapy) will be considered as confirmatory in the case of a fall in PSA, using previously published response criteria [22]. Where PET scan findings are recorded as positive, but the follow up refutes this, the scan will be recorded as false positive. Established RECIST (Vers 1.1) criteria will be used to interpret correlative imaging [23]. The details are as follows:

Follow up of clinical notes to 6 months will be performed for histopathological data, additional conventional imaging (CT, MRI and or bone scintigraphy), PSA change following focal salvage therapy (where no systemic therapy has been applied. Follow-up imaging will be performed by local read.

1. **Follow up histology**

Positive biopsy or histology will be taken to be confirmatory.

For negative biopsies: to rule out false negative imaging for image-guided biopsy will be reviewed. For lymph node biopsies, comparison of the PET/CT and follow-up (post intervention) imaging will be made to confirm that biopsy of the correct node occurred.

1. **Follow up imaging**

No established imaging criteria are available for a number of imaging modalities in recurrent prostate cancer. To enable comparison of these data with previous imaging trials, the imaging criteria as previously published by Fendler et al. will be used (§2.1.5.3 of Supplementary Materials 2: Trial Protocol [24])

1. **Follow up following local treatment**:

PSA change following radiation therapy will be according to previously published criteria, with a PSA response of > 50% taken to be confirmatory [25] (see figure 4).

[figure not shown]

**Fig.4.** Example interpretation criteria for patients undergoing biopsy or radiotherapy (with and without systemic hormone deprivation therapy) image from Emmett et al. [25]

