### Assessment of secondary outcomes

Tumour to background ratio will be compared for both tracers, as described previously in this protocol.

Confirmation for lesions will only be available where the patient’s condition dictates further clinical follow up, such as repeat imaging, or where histology is performed. This data will be collected, and as a secondary explorative outcome, follow-up for lesions rated as pathological will be done by composite follow-up standard of imaging, PSA and histology up to 6 months’ follow up. It is important to note that the performance of histology, further imaging or treatment is not a study specific intervention and is performed when considered clinically appropriate by the patient’s treating physician.

For n=10 individuals parametric imaging will be performed using standard parametric imaging analysis software with only descriptive statistics.

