### Primary Analysis

The primary outcome (proportion of patients with PSMA-positive pathological lesions) will be compared between tracers using an absolute risk difference (new tracer minus old tracer) with a one-sided lower 95% confidence interval (CI) for paired proportions (Wald with Bonett–Price Laplace adjustment). If the lower limit lies above -10%, we will claim non-inferiority. Proportion of pathologic scans will be based on majority consensus reads.

The number of PSMA-positive lesions defined as pathological, benign and uncertain in each region will be analysed using separate mixed-effects Poisson regression models with tracer as fixed covariate and nested random effects for patient and region. We will report incidence rate ratios with 95% CI and p-values. As a sensitivity analysis we will compare the number over all regions using the Wilcoxon signed-rank tests and the Mann-Whitney statistic with 95% CI.

Inter-reader reliability will be analysed on the region-level based on the number of benign, pathological and uncertain lesions determined by each reader. We will calculate Krippendorff’s alpha with a ratio difference function and bootstrap 95% CI separately for each tracer.

Lesion-based PPV will be calculated for each tracer as the proportion of pathological lesions confirmed pathological during follow-up among all lesions with a known state and will be presented with 95% Wilson score CI. Using all lesions with a confirmed status during follow-up, the two tracers will be compared using McNemar’s test and an absolute risk difference with 95% confidence interval.

The semi-quantitative tumour to background ratio will be summarized on a region-level (i.e. using the mean over all positive lesions per region) and analysed using a linear mixed-effects regression model with tracer as fixed covariate and patient and region as nested random effects. The mean difference with 95% CI will be reported.

For the subset of patients with additional parametric imaging data (N=10) the planned analysis of parametric imaging parameters (see first secondary endpoint) is planned prior to completion of the study. This exploratory analysis of this secondary endpoint will not assess the primary endpoint and will not influence further trial conduct or further trial process.

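### Any positive histology confirms a PET lesion, but the check that the biopsy hit its target is introduced only for negative biopsies and has no stated outcome, so PPV may be biased upwards

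*Protocol*

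**What the plan says.** Section 6.1.4 (Response Criteria, follow up histology) treats the two results differently.

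- **Positive result:** "Positive biopsy or histology will be taken to be confirmatory". No condition on the sampled site is attached.
- **Negative result:** "For negative biopsies: to rule out false negative imaging for image-guided biopsy will be reviewed". The sentence is garbled, but it evidently means that the imaging used to guide the biopsy is looked at again to see whether the result is a miss.
- **Lymph nodes, next sentence of the same paragraph:** "comparison of the PET/CT and follow-up (post intervention) imaging will be made to confirm that biopsy of the correct node occurred". The sentence does not itself say whether it is limited to negative node biopsies.

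The same section says what a refutation does: "Where PET scan findings are recorded as positive, but the follow up refutes this, the scan will be recorded as false positive". It does not say what becomes of a negative biopsy that the review finds to be off target.

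Section 11.4.2 (Primary Analysis) defines PPV as the "proportion of pathological lesions confirmed pathological during follow-up among all lesions with a known state". Histology is one part of the reference standard, which section 6.1.3 describes as a "composite standard of histology and/or correlative imaging as well as PSA-dynamics following external radiation therapy where available". Section 9.2.2 gives the endpoint's rank: "as a secondary explorative outcome, follow-up for lesions rated as pathological will be done by composite follow-up standard". Section 6.1.2.2 assigns the follow-up review to the principal investigator's team, unmasked.

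**The concern.** A reference standard should be checked in the same way whichever answer it gives. Here a refuting biopsy can be questioned on the ground that it sampled the wrong tissue, while a confirming biopsy at the same site is not questioned. If questioned negatives leave the PPV denominator and off-target positives stay in, errors are corrected in one direction only.

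The PPV of both tracers is at stake. To a smaller degree so is the difference between them, because the tracer with more false positives has more negative biopsies open to review. The protocol itself (section 3.4) reports more non-prostatic uptake with the new tracer and calls this clinically important. Because the reviewers are unmasked and no outcome rule is written, there is also room for discretion.

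**Working it through.** **Reading the text.** Of the five regions in section 5.2, two are nodal (pelvic and extra-pelvic lymph nodes) and three are not (prostate bed, bone, other organs).

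- If the node sentence applies to negative biopsies only, the check is one-sided in all five regions.
- If it applies to every node biopsy, the check is one-sided in the three non-nodal regions. For nodes, it then has to be reconciled with the unconditional rule for positives.

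On either reading, the target check depends on the result for at least part of the histology.

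**Model.** The protocol gives no expected PPV, biopsy rate or off-target rate, so there is no figure to reproduce and every input is an assumption:

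- p = true PPV among biopsied lesions
- h = probability that the biopsy samples the PET lesion
- q = probability that off-target tissue is malignant

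Misses are taken as independent of the lesion's true state, and on-target histology as correct.

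**Formulas for the observed PPV**

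1. No check, or off-target negatives reviewed but left as false positives: hp + (1−h)q
2. Off-target negatives set to unknown, off-target positives kept: [hp + (1−h)q] / [h + (1−h)q]
3. Same check on both results, failed matches unknown: hp / h = p

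The excess of (2) over p is (1−h)q(1−p) / [h + (1−h)q]. It is zero if q = 0, h = 1 or p = 1, and positive otherwise.

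**Results for formula (2)**

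| p | h | q | Calculation | Observed PPV | Bias (points) |
|---|---|---|---|---|---|
| 0.8 | 0.9 | 0.1 | 0.73 / 0.91 | 0.802 | +0.2 |
| 0.7 | 0.9 | 0.3 | 0.66 / 0.93 | 0.710 | +1.0 |
| 0.6 | 0.8 | 0.5 | 0.58 / 0.90 | 0.644 | +4.4 |
| 0.7 | 0.7 | 0.7 | 0.70 / 0.91 | 0.769 | +6.9 |
| 0.5 | 0.7 | 0.5 | 0.50 / 0.85 | 0.588 | +8.8 |

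Over p 0.6–0.9, h 0.80–0.95 and q 0–0.5, the bias runs from 0 to +4.4 points. The last two rows are the harsher case: 30% off target, with off-target tissue as often malignant as the PET lesion.

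**If off-target negatives stay as false positives (1).** At p = 0.7, h = 0.9, q = 0.3 the observed PPV is 0.63 + 0.03 = 0.66, a bias of −4.0 points. The direction therefore depends on the rule the protocol leaves out. Reviewing negatives is sound in itself, since it removes this downward error.

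**Difference between tracers under (2).** With common h and q, the observed difference is the true difference times h / [h + (1−h)q].

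- h = 0.9, q = 0.3: 0.9 / 0.93 = 0.968, so a 20-point gap reads as 19.4.
- h = 0.7, q = 0.3: 0.7 / 0.79 = 0.886, so it reads as 17.7.

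If q instead follows each tracer's own p (0.7 and 0.5) at h = 0.7, the gap is 76.9 − 58.8 = 18.1. With h = 0.9 and q = p/2 it is 71.1 − 51.4, about 19.8 before rounding (0.665/0.935 − 0.475/0.925).

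**The case against.** The strongest reply is that the text does not establish an upward bias. Five parts of it deserve an answer.

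- **Scope.** A reader might infer that biopsies are checked for target only when negative. The node sentence does not say so, and it can cover all node biopsies. This stands for the two nodal regions. It does not help the other three.
- **Consequence.** A reader might also infer that PPV is biased upwards as a matter of course. The protocol never says that off-target negatives are dropped, and if they remained false positives the bias could be downward. This stands. Dropping them is the natural outcome under a denominator of lesions with a known state, but it is not written.
- **Level of analysis.** For a region-based PPV (section 5.2), a positive neighbouring node in the same region legitimately confirms disease there. This stands, and it confines the concern mainly to lesion-level PPV (sections 5.3 and 9.2.3, and the lesion-based wording of section 11.4.2).
- **Hidden figure.** Figure 4 is not visible and may hold biopsy criteria. Its caption presents it as an example taken from a cited study, so it would not override the rule stated in the text.
- **Size and rank.** Plausible inputs give about one point. Histology is only part of a composite, obtained only where clinically performed, for an exploratory secondary endpoint. A lesion called on both tracers carries the same histology for both, so any effect on the difference comes from discordant lesions. All of this stands and limits the weight of the point.

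**Conclusion.** The concern holds in a limited form. As written, positive histology confirms unconditionally and the target review is introduced for negative biopsies. The scope for nodes and the consequence of a failed match are both left open. An upward bias in PPV is possible but not demonstrated. It requires that some off-target tissue is malignant and that off-target negatives are set to unknown.

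Under those conditions the bias is 0 to about 4 points among biopsied lesions over the main assumed range, and 7–9 points in the harsher case. It is diluted in the composite by the unstated share of lesions verified by imaging or PSA. The difference between tracers would shrink slightly. All these sizes rest on assumed rates. The primary non-inferiority comparison does not use follow-up and is unaffected. The point still merits action, because the asymmetry is in a stated rule, is applied by unmasked investigators, and is cheap to remove.

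**What to change.** Replace the two rules in section 6.1.4 with one that does not depend on the result. For all histology, positive or negative, compare the sampled site with the PET finding on the biopsy or post-intervention imaging. Require a match at the level of the analysis: same region for region-based PPV, same lesion for lesion-level PPV. Where the match fails, set the status to unknown in both directions. State explicitly that the node check covers all node biopsies.

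In the model above this returns the expected PPV to p. The cost is the review of a few positive biopsies by the team that already reviews the negatives, and a few positives may become unknown. Only adjudication changes. Patient management does not.
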